### Interim analyses {21b}

No interim analyses are planned. Data collection will end once all data have been collected in all study sites.

### Methods for additional analyses (e.g. subgroup analyses) {20b}

We will conduct the same analyses as described above (primary, secondary, and safety outcomes) stratified by vulnerable groups and by gender to explore whether the effect of the intervention differs between subgroups.

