**Methods:**

This study is an open-label, multi-centre, superiority, cluster-randomized controlled trial with two parallel arms (randomization 1:1 in at least 8 study sites) of a primary suicide prevention intervention based on psychoeducation versus an art-based control intervention. Four groups of youth aged 14–25 with high suicide risk will be recruited (in total, *n* = 240), including those (1) detained in juvenile detention centres, (2) disconnected from school, (3) in treatment for psychiatric disorders, (4) belonging to a sexual or gender diversity, (5) affected by chronic conditions, and (6) with relational/familial problems. Participants will be randomly assigned to the suicide prevention or control intervention. The primary outcome is suicide awareness measured on a validated scale. Secondary outcomes include knowledge of suicide, knowledge of local resources, suicidal behaviour, psychological distress, access to primary suicide prevention, and safety. Measures will be collected at baseline, at 1-week, and 3-month follow-ups. Analyses will be conducted as intention-to-treat using mixed-effects models.

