## Methods: participants, interventions and outcomes

### Study setting {9}

The study will take place in the French-speaking part of Switzerland. Vulnerable adolescents belonging to the following groups will be recruited for the study: (1) detained in juvenile detention centres, (2) disconnected from school, (3) in treatment for psychiatric disorders, (4) belonging to a sexual or gender diversity, (5) affected by chronic conditions, and (6) with relational/familial problems. The study includes both clinical and community sites (see study sites in Supplementary file 1).

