### Sample size {14}

Estimates for the sample size calculation (means, standard deviations, intraclass correlation, and effect size) are based on the results of the previous trial conducted with the same intervention in adolescents in Swiss secondary schools [19]. To estimate the effect size, we used data from the intervention group (*n* = 201 who participated at baseline and follow-up). This choice was driven by the significantly higher scores at baseline in the control group compared to the intervention group. The scores of the control group remained stable over time (mean = 23 at baseline and follow-up). The scores of the intervention group were lower at baseline but increased over time (mean = 21 at baseline and 24 at follow-up, sd = 6). This three-point difference on the 0–36 point scale was used as the effect size. The expected cluster size and cluster variability are based on the expected group sizes at the study sites (from 5 to 15 participants, with an average of 10 participants). With alpha = 0.05, power = 0.80, a two-sided test, an expected cluster size *k* = 10, variation coefficient (variation in the cluster size) = 0.5 (5 to 15 adolescents per cluster), ratio cluster = 1:1, intraclass correlation = 0.05, mean = 21 in the intervention group (standard deviation = 6), and mean = 24 in the control group (standard deviation = 6), we need *k* = 20 and *n* = 200. To account for attrition, we increased the sample size by 20% (*k* = 24, *n* = 240). Even though the study is a superiority RCT, we used a two-sided test of the difference between groups, to provide a conservative sample size, in line with the recommendations of Good Clinical Practice (GCP). The sample size was computed with Stata 18 using a test to compare two independent means in a cluster-randomized design.

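### Stratified reruns within vulnerable groups and genders do not estimate or test whether the intervention effect differs between them

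*Protocol article*

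**What the plan says.** The section on additional analyses (item 20b) repeats the primary, secondary and safety analyses "stratified by vulnerable groups and by gender to explore whether the effect of the intervention differs between subgroups". The analyses to be repeated are those under Statistical methods: mixed-effect linear or negative binomial models with the intervention as the treatment term, unadjusted and adjusted for baseline characteristics, and run separately at 1 week and 3 months for the secondary scales. Neither place gives a treatment-by-subgroup term or any other comparison of effects between strata.

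Study setting lists six vulnerable groups, ending with "5) affected by chronic conditions, and (6) with relational/familial problems". Type of vulnerable population is listed under Study site information, so it is recorded per site. Clusters are randomized 1:1 within site in blocks of two. The sample size covers the overall comparison only: "With alpha = 0.05, power = 0.80, a two-sided test", ICC 0.05, and 20 clusters (200 participants) raised to 24 clusters (240 participants) for attrition. Item 20a plans a Bonferroni-Holm adjustment for multiple testing but does not define the families of tests.

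**The concern.** The stated question is whether the effect differs between subgroups. The stated method gives one effect per subgroup. To answer the question, the effects have to be compared with each other, with a standard error for the comparison, and a set of separate analyses does not supply that. What separate analyses do supply is a list of estimates and p values, which invites the reader to treat groups with p below 0.05 as responders and the others as non-responders.

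With few clusters per group, such a pattern is likely to arise by chance even when the effect is the same everywhere. A paper could then suggest that the workshop helps some vulnerable groups and not others when the data cannot show it. Few clusters also make the models themselves fragile: a between-cluster variance and site-level covariates cannot be estimated reliably from about four clusters.

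**Working it through.** **Inputs** (Sample size, item 14)
- Effect: 3 points, since the difference on the 0–36 "point scale was used as the effect size".
- SD 6: "mean = 21 at baseline and 24 at follow-up, sd = 6".
- Cluster size m = 10: "from 5 to 15 participants, with an average of 10 participants".
- "variation coefficient (variation in the cluster size) = 0.5".
- ICC 0.05; 24 clusters; 20% attrition.
- Six categories (Study setting, item 9).

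**The plan's own figure.** Unclustered n per arm = 2 × (6 × (1.96 + 0.84)/3)² = 62.8. Design effect with unequal clusters = 1 + ((1 + 0.5²) × 10 − 1) × 0.05 = 1.575. Then 62.8 × 1.575 = 98.9 per arm, or 9.9 clusters, rounded up to 10 per arm. This gives 20 clusters and 200 participants, and × 1.2 gives 24 and 240. The stated figures reproduce.

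**One vulnerable group.** Assumption: group is the site-level type and the clusters are spread evenly. 24/6 = 4 clusters, so 2 per arm.
- No attrition, 10 per cluster: SE = 6 × √(2 × 1.575/20) = 2.38.
- 8 analysed per cluster: design effect 1 + (1.25 × 8 − 1) × 0.05 = 1.45, and SE = 6 × √(2 × 1.45/16) = 2.55.

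| | 10 per cluster | 8 per cluster |
|---|---|---|
| SE | 2.38 | 2.55 |
| 95% CI half-width, normal (1.96 × SE) | 4.7 | 5.0 |
| 95% CI half-width, t with 2 df (4.303 × SE) | 10.2 | 11.0 |
| Power for 3 points, normal | 24% | 22% |
| Power for 3 points, noncentral t, 2 df | 12% | 11% |

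**Same 3-point effect in all six groups, unadjusted tests.** P(mixed pattern) = 1 − p⁶ − (1 − p)⁶, where p is the power in one group.
- Normal: p = 0.243 gives 0.81; p = 0.217 gives 0.77.
- t, 2 df: p = 0.121 gives 0.54; p = 0.112 gives 0.51.

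**The same with Holm across the six groups, normal.** Holm rejects at least once only if the smallest p value is below 0.05/6, that is |z| > 2.638. The chance per group is Φ(3/2.38 − 2.638) = 0.084, or Φ(3/2.55 − 2.638) = 0.072. P(at least one) = 1 − 0.916⁶ = 0.41, or 1 − 0.928⁶ = 0.36. The chance that all six are rejected is about 0.0002 or less, so these are also the mixed-pattern probabilities.

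**No effect anywhere.** P(at least one significant group) = 1 − 0.95⁶ = 0.265 unadjusted, and at most 0.05 with Holm across the six.

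**What the interaction test can do** (10 per cluster, normal).
- One group against another: SE = √2 × 2.38 = 3.37; power for a 3-point difference about 14%; detectable with 80% power: 2.80 × 3.37 = 9.4 points.
- One group against the other five: SE of the effect in the five (10 clusters per arm) = 6 × √(2 × 1.575/100) = 1.065; SE of the difference = √(2.38² + 1.065²) = 2.61; power about 21%; detectable difference 7.3 points.
- With 8 per cluster, power is about 13% and 19%.

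**The case against.** The strongest reply is that the analysis is only meant to explore, that stratified estimates with intervals are common in exploratory reporting, and that the analysis plan, to which the article defers analytical detail, may add an interaction. The exploratory label does limit the seriousness. It does not make the method answer its question: the article itself ties the question of differing effects to stratified reruns, so an analysis plan that follows this sentence carries the gap forward.

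Several stronger readings are tempting, and the document does not support them.
- A reader might infer that the trial will compare which strata are significant. No such rule is stated. The mixed-pattern probabilities show what would happen if results were read that way.
- Two clusters per arm is not a planned number. It is an average under even spread; some categories may have more clusters and others fewer.
- A single figure such as 77% for a mixed pattern, or 26.5% for a false-positive group, ignores both the t-based results and the planned Holm adjustment. Because the families are undefined, the range should be shown.
- The figures do not carry over to gender, which does not divide whole clusters.
- Membership may overlap at person level, for example psychiatric treatment and sexual or gender diversity. If personal status defined the strata, they would cut across clusters and the count of four would not hold. The two criticisms cannot be made together.
- Safety is planned as percentages with CIs and standardized mean differences, with no inferential test for serious events, so the point concerns the efficacy outcomes.
- The Discussion speaks of targeting vulnerable subgroups of adolescents. This may mean vulnerable youth in general and need not mean choosing among the six categories.

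It is also fair to say that an interaction test is weak here. That stands as a limit of the remedy; it is no argument for the stratified reruns.

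**Conclusion.** The point holds as a mismatch between the stated question and the stated method, for both vulnerable group and gender: separate analyses per stratum give no estimate or test of a difference in effect. This part needs no assumption.

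The numerical part applies to vulnerable groups only. It rests on the site-level definition, even spread of the 24 clusters over six categories, and the protocol's SD, ICC and cluster sizes. Under these, a stratum is too small for a reliable mixed model or a useful estimate, and differing significance across groups is a likely result of a uniform effect, less so with Holm but still in more than a third of trials. It is worth correcting, but it concerns an exploratory analysis and does not affect the primary result.

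The Abstract's "Four groups of youth aged 14–25 with high suicide risk will be recruited", followed by a list of six, is a clerical slip and has no bearing on the conclusion.

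**What to change.** For the efficacy outcomes, replace the stratified reruns by one mixed model on all participants with an arm × subgroup term, fitted once for site population type and separately for gender. Report the interaction estimate or test, and the subgroup effects with confidence intervals from that model. Label them exploratory and make no within-stratum significance claims. State that vulnerable group means the site's population type, if that is what is intended.

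The cost is wording in the protocol and the analysis plan; no data collection changes. There are two downsides. Per-group reporting becomes less detailed. The interaction test keeps low power, about 14 to 21% for a 3-point difference, so a non-significant interaction must not be read as evidence that the effect is the same in all groups.

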### Methods in analysis to handle protocol non-adherence and any statistical methods to handle missing data {20c}

We will first describe patterns of missing values (see the section Statistical methods for primary and secondary outcomes {20a}, subsection ‘O8’). In case of missing values at baseline, we will use MICE. Missing values on the outcomes will be handled by MICE (for intention-to-treat analyses) and inverse probability attrition weighting to correct our estimates for attrition [43, 44]. We will also use tipping point analysis under the missing not at random assumption to test the robustness of our findings [45]. The statistical analysis plan will provide details on the analytical strategy.

### Plans to give access to the full protocol, participant-level data and statistical code {31c}

All study documents, including the study protocol, de-identified participants’ data, and statistical codes, will be accessible through the SWISSUbase repository.

### Oversight and monitoring

#### Composition of the coordinating centre and trial steering committee {5d}

The sponsor is [name]. The principal investigators (PIs) are [name] and [name]. [name] is also the Central Data Monitor, while [name] is the statistician. The monitoring institution is the Clinical Trial Unit at the University of Bern, Switzerland. The steering committee include co-authors of this protocol. In the event of study-related damage or injuries, the liability of the University of Lausanne provides compensation, except for claims that arise from misconduct or gross negligence.

#### Composition of the data monitoring committee, its role and reporting structure {21a}

This is a multi-centre trial that does not require a data monitoring committee, as this is a low-risk intervention.

#### Adverse event reporting and harms {22}

As the intervention has previously been shown as acceptable [19], we do not expect SAEs related to the study intervention. The potential discomfort created by the discussion of suicide will be handled by the psychologist, and information on local resources will be given to all participants. The study sites serve populations with high suicide risk. Suicide attempts and deaths by suicide may occur during the study period, as they do outside the study period in this population. The study sites have specific procedures for dealing with such events. In addition, we will train all staff at the study sites (e.g. medical, educational, prison staff). The intervention for the staff will be an awareness session (‘module de sensibilization’) of a standardized suicide prevention intervention for professionals given by suicide prevention experts (Groupe Romand Prévention Suicide, Stop Suicide, University of Lausanne) [46]. If a suicide attempt or a death by suicide occurs during the study period and up to 1-month post-baseline, contact will be made between the local professional team and the suicide prevention experts to determine which additional support is needed. Interventions include debriefing, group support, and specific postvention interventions for the youth and the professional team.

Several characteristics of the SAEs will be reported to the Sponsor-Investigator within 24 h, including time, duration, severity, and outcome of the event, action implemented, and link to the study participation. SAEs will be reported within 15 days to the Ethics Committee if it cannot be excluded that their occurrence is related to the ongoing study.

#### Frequency and plans for auditing trial conduct {23}

The Clinical Trial Unit at the University of Bern will conduct two site monitoring visits during the study period. Auditors conducting these visits, the Ethics Committee as well as cantonal authorities will have access to all documents and data from the study. In addition to these planned audits, a site initiation visit will be organized by the sponsor at the beginning of the study.

#### Plans for communicating important protocol amendments to relevant parties {25}

The study protocol can be amended by the Sponsor and PIs of the study. Substantial protocol amendments are submitted to the Ethics Committee for approval. In case of an emergency, deviations from the initial protocol are allowed to protect participants’ safety, rights, and wellbeing without prior Ethics Committee approval. These deviations will be reported to the Ethics Committee in the shortest possible time.

#### Dissemination plans {31a}

Research findings will be published in leading international peer-reviewed journals. One doctoral thesis will be conducted in the project. Students in medicine will also be involved in the project (master thesis and dissertation).

Data will be available for re-use after the publication of the main paper. A responsible person will approve new research proposals to avoid overlapping analyses/manuscripts.

## Discussion

The study will fill an existing research gap and provide evidence of the potential benefits of a brief primary suicide prevention intervention for vulnerable adolescents and young people. It will provide robust, evidence-based results to guide interventions to support adolescents and target vulnerable subgroups of adolescents, including evidence-based recommendations for clinical management and public health. A confirmed beneficial effect may influence recommendations for suicide prevention and lead to sustainable advances in primary suicide prevention. Indeed, the health care system should provide timely suicide prevention interventions and remove systematic barriers to adequate prevention in all groups, including vulnerable young people. The project will also fill research gaps in suicide prevention in Switzerland and thus provide an opportunity to improve suicide prevention [47].

The results of this trial project may have a substantial impact on suicide prevention by addressing the question of the benefits of primary suicide prevention for vulnerable adolescents. Strengths of this proposal include (1) unique collaboration between clinicians, epidemiologists, suicide prevention experts, social scientists, and education specialists and involvement of international experts; (2) use of a gold standard design; (3) use of a proven intervention; and (4) good statistical power.

Knowledge transfer will be ensured in the field of prevention and among professionals working with young people. We plan to disseminate the results to organizations involved in health promotion and prevention, as well as training for health professionals, school health promotion services, and public health centres and authorities. Knowledge transfer will include dissemination through written information and participation in workshops on adolescent suicide prevention. The involvement of international partners may also lead to the replication of the study in other countries and contribute to the formation of international networks that strengthen research, practice, and policy on suicide prevention for vulnerable adolescents.

Overall, this project aims to fill the current gap in high-quality evidence on primary suicide prevention among vulnerable young people. The findings may have significant policy implications by providing evidence-based support for decisions on primary suicide prevention and the protection of vulnerable young people. The results will provide decision-makers with the data needed to strengthen policies aimed at preventing suicide and protecting vulnerable young people. As suicide prevention organizations are involved in this project, the transferability of the project’s findings to fieldwork and clinical practice will also be facilitated.

### Trial status

This manuscript refers to version 6 of the protocol (August 19, 2025). Participant recruitment will start in January 2025 and is planned to be completed by June 2027. The study is expected to be completed by September 2028. The trial is registered on ClinicalTrials.gov (ID NCT06551038, registered on August 13, 2024). We used the SPIRIT checklist and the World Health Organization Trial Registration Data Set.

## Data Availability

The Case Report Form (French version) is available upon request to the corresponding author.

## Abbreviations

AE: Adverse event
ESPAIR: Evaluating primary suicide prevention in adolescents with risk factors
GCP: Good Clinical Practice
K-6: Kessler Psychological Distress scale
LOSS: Literacy of Suicide Scale
MICE: Multiple imputation by chained equations
PSAS-9: Nine-item perceived suicide awareness scale
SAE: Serious adverse event
SIDAS: Suicidal Ideation Attributes Scale
SPIRIT: The Standard Protocol Items: Recommendations for Interventional Trials
